# Effect of a resistance and balance exercise programme for women with osteoporosis and vertebral fracture: study protocol for a randomized controlled trial

**DOI:** 10.1186/s12891-018-2021-y

**Published:** 2018-04-03

**Keywords:** Osteoporosis, Vertebral fracture, Exercise, Physical function, Health related quality of life

## Abstract

**Background:**

Osteoporotic vertebral fractures are common, and are associated with reduced functioning and health related quality of life. The primary aims of this randomized controlled trial are to examine the immediate and long-term effects of a 12-weeks supervised group exercise programme on habitual walking speed in older women with osteoporosis and a history of vertebral fracture. The secondary aims are to examine the immediate and long-term effects of the exercise program on physical fitness, fear of falling and quality of life.

**Methods:**

The study is a single-blinded randomized controlled trial. Women aged 65 years or older with osteoporosis and a history of vertebral fracture are included. The intervention group receives a 12-week multicomponent exercise programme, including resistance training combined with balance training. The control group receives usual care. Adherence to the programme will be of importance for the internal validity of the study. Participants in the exercise group who don’t attend will be followed up with motivational phone calls. The primary outcome is habitual walking speed over 10 m. Secondary outcomes are health related quality of life (Qualeffo-41, SF-36), physical activity (I-PAQ), Patient Specific Functional Scale, Fear of falling (FES-1) and physical fitness (Senior Fitness test, Functional reach test, 4 square step test, grip strength). Sample size, based on the primary outcome, is 150 participants randomized into the two arms on a 1:1 allocation, including an estimated 20% drop out. Descriptive data will be reported as mean (standard deviation), median (range) or count (percent) as appropriate. The data will be analysed following the intention-to-treat principle. Between group differences in primary and secondary outcomes at 3 months follow-up will be assessed using linear regression models with respective outcome at baseline as covariate and the randomised group as factor.

**Discussion:**

This trial will generate new knowledge on the effects of a multicomponent exercise programme among women over 65 years with osteoporosis and a history of vertebral fracture, knowledge that is of importance for clinicians, health managers and policy makers.

**Trial registration:**

ClincialTrials.gov Identifier: NCT02781974. Registered 18.05.16. Retrospectively registered.

## Background

Osteoporosis is a worldwide health problem. Approximately 30% of all postmenopausal women in Europe and the United States have osteoporosis. More than 40% of these women will sustain one or more fragility fractures in their remaining course of life [1] Osteoporosis is usually defined as an overall bone mineral density (BMD) that is less than or equal to 2.5 standard deviations below the mean BMD for young, female adults [2]. The prevalence of osteoporosis is more frequent among women than men [2]. Osteoporosis is a systemic skeletal disease characterised by low bone mass and deterioration of bone tissue leading to bone fragility and an increased risk of fractures [2].

An osteoporotic fracture, also called a fragility fracture, is a fracture that occurs with minimal trauma [3]. Vertebral fractures, the most common type of osteoporotic fractures, are associated with height loss, kyphosis, back pain and reduced balance, mobility and activity of daily life (ADL), as well as reduced physical activity [4, 5]. Women with osteoporotic vertebral fractures have an increased risk of subsequent vertebral fractures [6] and experience reduced health related quality of life (HRQOL) compared to those who have not experienced fractures [2, 7, 8]. Several studies have shown that people with vertebral fractures experience reduced HRQOL, both in short and long term perspective [9–11]. Further, women with fragility fractures are more likely to experience fear of falling, anxiety, depression and loss of social roles [12–15].

Good physical fitness can contribute to maintenance of functional independence in older people [16]. According to Rikli and Jones [17] physical fitness is defined as the capacity to perform activities of daily living safely and independently without fatigue. The concept is multidimensional and includes muscle strength, aerobic endurance, flexibility, body composition, dynamic balance and agility/mobility [17]. Recent recommendations specify that older adults with osteoporosis or osteoporotic vertebral fractures should engage in a multicomponent exercise programme that includes resistance training combined with balance training [18, 19]. The mode of exercise, dosage and effects on different outcomes for this group has not yet been well established by research [3, 20]. Safety considerations are necessary when it comes to exercise for individuals with vertebral fractures since adverse events have happened in previous randomized trials [3, 18, 19]. Examples include modifying or avoiding rapid, repetitive, weighted and sustained or end-range flexion or twisting of the spine [18, 21]. Although individual trials of exercise in individuals with vertebral fractures did report benefits for some pain, physical function and quality of life outcomes, the quality of evidence is low. A recent Cochrane review concluded that there is insufficient evidence to determine whether exercise interventions reduce fear of falling beyond the end of the intervention, and their effect on other outcomes from designed randomised trials is required [22]. However, Olsen and Bergland [23] concluded that a group-based exercise programme and an educational session had a positive and durable effect on fear of falling in community-dwelling elderly women with osteoporosis and a history of vertebral fracture.

The main focus of this project is to develop evidence-based knowledge regarding exercise as an intervention for improving physical fitness and HRQOL in older women with osteoporosis and a history of vertebral fracture. Finding safe and feasible interventions to improve physical fitness and increase HRQOL in this group will have great potential benefits. This study builds on a previous study conducted by Bergland et al. [24]. However, the intervention in this study will to a greater degree conform to recent exercise recommendations regarding dosage and difficulty level [18]. In this trial we have left out the education component to be able to explore solely the effect of exercise, and we aim to include a larger sample.

### Aims

#### Primary aim

To assess the effects of a 12-weeks supervised strengthening and balance programme on habitual walking speed among older women with osteoporosis and a history of vertebral fracture.

#### Secondary aims

To assess the effects of the same programme on physical fitness, fear of falling and health related quality of life among women with osteoporosis and a history of vertebral fracture.

### Hypotheses

An intervention consisting of a 12- weeks supervised group exercise programme will improve habitual walking speed as well as physical fitness, fear of falling and quality of life among older women with osteoporosis and a history of vertebral fracture.

## Methods/design

### Study design

This is a parallel-group, single blinded randomized controlled trial. The participants will be randomly assigned in a 1:1 ratio to the intervention group and the control group after baseline assessment. A computer-generated, permuted block randomization scheme is used to allocate the participant, block sizes varying from 4 to 8. The allocation of the participants is administered by an individual not involved in any testing or contact with the participants, and the allocation sequence is kept on that individual’s computer. Following randomisation, the participant receives information by telephone on which group they are allocated to. See flow chart in Fig. 1.

**Fig. 1 Fig1:**
[figure not shown]
Flow of participants in the study

### Study setting

The present study will be undertaken at facilities in Oslo and Akershus University College of Applied Sciences, and at two different community based facilities in the area around Oslo, Norway.

### Recruitment and study population

Participants will be recruited from a specialty outpatient clinic for osteoporosis in Oslo, and from two outpatient clinics at hospitals in and around Oslo.

### Exclusion/inclusion

We will include women at the age of 65 or over, living at home and able to walk independently with or without walking aid. Further, to be found eligible, the women must have a t-score − 2.5 SD or less verified by Dual X-ray Absorptometry (DXA) scan and at least one vertebral fracture classified grade 1, 2 or 3 [6] verified by DXA or X-ray. Patients will be excluded if they are not able to speak and understand Norwegian. Individuals who have self-reported severe diseases or other health conditions like severe lung- or heart diseases that make it unsafe to exercise will be excluded. In cases of uncertainty the participants will be asked to consult their physician to make sure that it is safe for them to exercise.

### Intervention group

The intervention will be informed by recent exercise recommendations for people with osteoporosis and vertebral fracture [18], which recommend progressive resistance training for all major muscle groups in combination with balance training. The expert panel recommends that older people with osteoporosis and vertebral fracture do not engage in aerobic exercise to the exclusion of resistance and balance training [18]. The recommendations for exercise prescription for people with osteoporosis and vertebral fracture are based on the GRADE process [3] to evaluate the quality of existing evidence and generate recommendations for exercise prescription [18]. The programme should be performed at a minimum of twice a week. Alongside with the mentioned recommendations [18], the exercise program of this study is also based on the guidelines from the position stand on Exercise and Physical Activity for Older Adults from the American College of Sports Medicine [25], recommendations for fall prevention exercises [26] and guidelines for treatment in postmenopausal and senile osteoporosis [27].

The intervention is designed as a group-based circuit exercise programme of eight different exercises. Emphasis is put on resistance and balance exercises with some aerobic components as well. The majority of the exercises will be carried out in a weight bearing position, with or without support. Besides different exercises to improve leg strength and balance, exercises for upper limb strength, upper and lower back strength and posture are also integrated in the programme. The intervention will be led by an experienced physiotherapist. The participants with increased risk of falls, restrictions in movement or weight-bearing during training and activity will be focused upon to avoid injuries. The physiotherapists will be trained in instructing the resistance and balance exercise programme and to make sure the participants have support objects nearby when necessary.

The programme will last for 1 h and will be carried out twice a week for 12 weeks. The physiotherapist supervising the exercise session, will also be responsible for individual tailoring and suitable dosage and progression of the exercises. The exercise session starts with 10 min warm up consisting of stretching, breathing exercises, flexibility and dynamic balance carried out with background music. The warm up is followed by two rounds of stationary circuit sessions with strength- and balance exercises. The participants will work 1.5 min at each station, with a short break of 30 s to rest and move to the next station. The exercise session ends with 10 min cool down and stretching. The participants are encouraged to report any serious adverse events caused by the exercise like muscle soreness, joint tenderness and increased level of pain.

When designing the exercise programme all the chosen exercises were evaluated according to safety cautions for people with osteoporosis and vertebral fractures [3, 18, 21]. Exercises that includes flexion and rotation of the spine are not considered safe and therefore not included in the programme. We also had in mind that the participants should be able to support themselves on a chair or a bar when performing exercises that challenged the balance if needed. Correct techniques in the different exercises is also a priority in the programme, and for the two first weeks of the programme this is emphasized for the participants by thoroughly instructions of the physiotherapists. The exercise group will have no more than 8–10 participants at the time, making sure that the physiotherapist can supervise and instruct the participants in a safe way. After a few weeks of adaption, the participants are encouraged to intensify their exercise and work until volitional fatigue without jeopardizing safety so that they perceive it as somewhat hard. This corresponds with an intensity level of 13–14 on the Borg Rating of Perceived Exertion Scale [28]. Weight belts, elastic bands, manual weights and frequency will be used for the progression of the strength exercises. Advancing to more challenging positions will be used to progress in balance exercises [29]. See Table 1 for a detailed description of the exercises.

**Table 1 Tab1:** Resistance and balance programme, description of exercises

Exercise	Therapeutic goal	Level	Description	Progression or modify
Squats	Leg strength	1	Raise from a chair (sit to stand)	Tempo, weightbelt
		2	Deep squats (lower than 90 degrees kneeflexion)	Weightbelt, Degrees of kneeflexion
		3	Lounges	Weightbelt
Step up	Leg strength, dynamic balance	1	Go up and down from a step, change legs	Height of steps, tempo, Weightbelt. support
		2	Step up and one leg stance, go down	Tempo, height of steps
Sideways step up	Hip stability, dynamic balance, leg strength	1	Step up sideways on a step	Height of the step, tempo, weightbelt
Upright row	Posture, upper back strengthening	1	Row exercise with elastic bands	Three different resistance levels on the elastic bands
Balance pad	Balance, static and dynamic	1	Standing on balance pad, semitandem	Open/closed eyes, turning head from one side to the other
		2	Standing on balance pad, tandem	
		3	One leg standing	
Chest press	Chest and arm strengthening	1	Chest press against the wall	
		2	Chest press against a bench	
		3	Chest press resting on the knees on the floor	
Hip raise	Lower back strengthening	1	Lying on back with knees bent, raise hip	
		2	One leg hip raise	
Diagonal lift		1	Standing on all four, lift left arm and right leg, alternate	Choose either hip raise or diagonal lift
Biceps curl	Upper arm strengthening	1	Seated armcurls with dumbbells	Increase load of dumbbells (1, 2, 3, 4 or 5 kg)

### Control group

Participants allocated to the control group receive treatment as usual. They are asked to maintain their current physical activity level and continue life as usual. They will be contacted for their follow up tests at 3 months and 6 months. After the 6-months test, participants in the control group are offered to participate in the same strength and balance exercise programme as the participants of the intervention group.

### Time plan of the study

Recruitment started January 2016 and is expected to be completed by spring 2018. The intervention will continue 12 weeks after the last inclusion. Data collection will last for 6 months after recruitment is completed. Thereafter, we will write up and publish peer-reviewed articles.

### Outcome measures

Assessments will be performed at baseline, and at 3 and 6 months. The participants are randomised after the baseline assessment by a person not involved in the recruitment, assessment or intervention of the study. Assessors (certified physiotherapists) are blinded to participants’ group allocation for all outcomes and the participants are instructed not to reveal group allocation to the assessors during the study period. The assessors are taking part in a training programme to ensure consistency in how the tests are performed and to ensure that the protocol is standardized. The time window between baseline assessment and start of intervention is aimed to be within two week(s) and the same time window for assessment due at 3 and 6 months.

### Adverse events

Adverse events such as falls, pain, fracture, and joint pain will be recorded by the instructor of the group during the exercise sessions. The participants will be instructed to report any adverse events outside the exercise session to the instructor of the group.

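### Falls, fractures and other non-pain adverse events are captured only through the exercise-class instructor, so the two arms are ascertained unequally

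*Protocol article*

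**What the plan says.** The Adverse events section of the protocol article has two sentences and one mechanism. The first covers events in class: "Adverse events such as falls, pain, fracture, and joint pain will be recorded by the instructor of the group during the exercise sessions". The second covers events elsewhere: "The participants will be instructed to report any adverse events outside the exercise session to the instructor of the group". The Intervention group section adds one further statement, limited to events attributed to the training: "The participants are encouraged to report any serious adverse events caused by the exercise like muscle soreness, joint tenderness and increased level of pain".

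The Control group section says: "Participants allocated to the control group receive treatment as usual". On contact it says: "They will be contacted for their follow up tests at 3 months and 6 months". Controls may join a class later: "After the 6-months test, participants in the control group are offered to participate in the same strength and balance exercise programme". The schedule is the same for both arms: "Assessments will be performed at baseline, and at 3 and 6 months". The exercise sessions themselves run for 12 weeks.

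The Background gives the reason for attention to harm: "Safety considerations are necessary when it comes to exercise for individuals with vertebral fractures since adverse events have happened in previous randomized trials". It also names safe and feasible interventions as a goal of the work.

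**The concern.** The recorder and the recipient of reports are the same person, and that person exists for one arm only. Women with osteoporosis and a vertebral fracture can fall or fracture without any exercise; the Background itself notes their raised risk of further vertebral fracture. A count from exercisers alone therefore mixes harm from the programme with events that would have happened anyway. If that count were set beside whatever emerged incidentally from controls, the difference would partly or wholly reflect who was asked.

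At stake is what the trial can say about safety, not its result on walking speed. The matter is more than brevity in an article: the method of ascertainment is stated, and as stated it is tied to the class. A later analysis plan cannot analyse events that were never collected.

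**Working it through.** No stated figure needs reproducing. The check is a reading of every section that could supply events from each arm, followed by an illustration of size.

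**Routes described, by arm and period**

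| Source (section) | Exercise, weeks 1–12 | Exercise, after week 12 to month 6 | Control, to month 6 |
|---|---|---|---|
| Instructor records in session (Adverse events) | yes | no sessions | no sessions |
| Report to instructor (Adverse events) | yes | no end date given, but no contact described | no instructor |
| Events caused by exercise (Intervention group) | yes | not described | cannot apply |
| Event enquiry at 3- and 6-month tests (Control group; Outcome measures) | not described | not described | not described |
| Falls and fall injuries in the last year (Demographic variables) | no follow-up repeat stated | no follow-up repeat stated | no follow-up repeat stated |
| Pain in QUALEFFO-41 and SF-36 (Health-related quality of life) | yes | yes | yes |

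Two possible rescues:

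- Reading the participants in the Adverse events section as all randomised women does not help. The recipient is still the group's instructor, whom controls can meet only after the 6-month test.
- Repeating the last-year falls question at 3 or 6 months would reach back before randomisation, and fractures have no item of their own there.

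Pain does survive the check, because it is measured in the same way in both arms.

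**Size, for illustration only**

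The document supplies 150 women allocated 1:1, so 75 per arm. The true risk p (equal in both arms), 90% capture in the exercise arm and control capture c are assumptions.

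Expected recorded counts are 75 × 0.9p and 75 × c × p. The apparent risk ratio is 0.9/c, whatever p is.

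- c = 90%: 0.9/0.9 = 1.0, so there is no distortion.
- c = 50%: 0.9/0.5 = 1.8. At p = 20% the counts are 75 × 0.18 = 13.5 and 75 × 0.10 = 7.5.
- c = 25%: 0.9/0.25 = 3.6. At p = 20% the counts are 13.5 and 75 × 0.05 = 3.75.

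The chance of a spurious two-sided 5% difference uses the normal approximation Φ[(d − 1.96·se₀)/se₁]. Here d is the difference in recorded proportions, se₀ its pooled and se₁ its unpooled standard error. For true risks of 10%, 20% and 30%:

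- c = 50%: about 16%, 29% and 44%.
- c = 25%: about 40%, 71% and 89%.

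These counts are small. Summing the binomial probabilities of all tables with Fisher's exact p < 0.05 gives lower values: about 9%, 22% and 36% at c = 50%, and about 26%, 65% and 86% at c = 25%. The direction is unchanged.

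The extreme case is full capture in one arm and none in the other. With an assumed 15% falling in each arm, 75 × 0.15 ≈ 11 against 0 gives Fisher p = 0.00066. With 8%, 6 against 0 gives p = 0.028.

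**The case against.** The strongest reply is that the document never promises the comparison at risk. Falls, fractures and adverse events are not among the aims or the listed outcomes, and the Statistical procedure section applies its between-group models to primary and secondary outcomes only. The Adverse events section can be read as a safety log for the intervention. This stands, and it limits the severity.

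It is also fair to say that an article condenses a fuller protocol, and that an event enquiry at the follow-up tests could be written there. That has some force for details of the visits. It does not remove the difficulty that the mechanism actually stated serves one arm.

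Several stronger readings are tempting, and the text does not carry them:

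- A reader might infer that controls are contacted solely for their tests. The Control group section does not say so, and the Study design section describes a telephone call about allocation.
- A reader might infer that the plan excludes events from month 3 to month 6 in both arms. The instruction to report to the instructor has no end date; what can be said is that no route is described after the programme ends.
- A reader might infer that no safety comparison of any kind is possible. Pain is measured alike in both arms.
- A reader might take 11 against 0 as what the trial will record. That needs an assumed event rate, complete unprompted reporting by exercisers and none by controls. Only the arithmetic is firm.

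**Conclusion.** The concern holds for falls, fractures and other non-pain adverse events. As described, their ascertainment depends on an instructor whom controls do not have during follow-up and whom exercisers no longer meet in class after 12 weeks. Counts from the exercise arm cannot be told apart from background, and a two-arm table would tend to show exercise as more harmful by roughly the ratio of capture: 1.8 at 90% against 50%, and 3.6 at 90% against 25%. Those capture rates and all event rates are assumptions. The conclusion about unequal ascertainment rests on the text and does not need them.

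Severity is moderate. Pain can still be compared, the primary analysis is untouched, and no between-arm safety test is planned. What is limited is any conclusion about harm, in a trial that gives safety as part of its motivation.

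**What to change.** At the existing 3- and 6-month visits, give both arms the same short self-completed form on falls, fractures and other adverse events since the last visit. Have it returned so that the blinded assessor does not see it, for example in a sealed envelope or to study staff who already know the allocation. Base any between-arm safety statement on this form. Report the instructor's log separately, as information on the exercise arm only.

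For women who have already passed these visits, either confine safety statements to the exercise arm or state the incomplete coverage.

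The cost is one page at visits that already take place, with two downsides. Recall over three months is less complete than recording in session, although the enquiry is the same in both arms. Coverage is also partial if the form comes late: recruitment began in January 2016, was due to end by spring 2018, and the article appeared in April 2018. If recruitment had been even over those roughly 27 months (an assumption), a form introduced at publication would reach about 6/27 = 22% of the women recruited by then at their 6-month visit, and about 3/27 = 11% at their 3-month visit.
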